## Abstract

**Background:**

Workers in wet work occupations have a risk for developing hand eczema. Prevention strategies exist, but compliance to the proposed recommendations is poor. Therefore, a multifaceted implementation strategy (MIS) is developed to implement these recommendations to reduce hand eczema among health care workers performing wet work.

**Methods/Design:**

This study is a randomised controlled trial in three university hospitals in the Netherlands. Randomisation to the control or intervention group is performed at department level. The control group receives a leaflet containing the recommendations only. The intervention group receives the MIS which consists of five parts: 1) within a department, a participatory working group is formed to identify problems with the implementation of the recommendations, to find solutions for it and implement these solutions; 2) role models will help their colleagues in performing the desired behaviour; 3) education to all workers will enhance knowledge about (the prevention of) hand eczema; 4) reminders will be placed at the department reminding workers to use the recommendations; 5) workers receive the same leaflet as the control group containing the recommendations. Data are collected by questionnaires at baseline and after 3, 6, 9 and 12 months. The primary outcome measure is self-reported hand eczema. The most important secondary outcome measures are symptoms of hand eczema; actual use of the recommendations; sick leave; work productivity; and health care costs.

Analyses will be performed according to the intention to treat principle. Cost-effectiveness of the MIS will be evaluated from both the societal and the employer's perspective.

**Discussion:**

The prevention of hand eczema is important for the hospital environment. If the MIS has proven to be effective, a major improvement in the health of health care workers can be obtained. Results are expected in 2014.

**Trial registration number:**

NTR2812

## Background

Occupational skin diseases are considered to be in the top-3 of work-related disorders in Europe [1]. Hand eczema accounts for 90% of the occupational skin diseases [2]. One of the most important risk factors for developing hand eczema is exposure to irritants [1]. Water, soap, cleaners, detergents and solvents are among the most common irritants [1,3]. As a consequence, workers who handle these irritants in their work have a higher risk to develop hand eczema [3]. Because of this, especially nurses are at risk for developing hand eczema [3,4]. In a recent study in the Netherlands, the 1-year prevalence of self-reported hand eczema among health care workers, including cleaners, in a university medical hospital was 24% [5]. In comparison, in the general population the 1-year prevalence is nearly 10% [6]. In addition, other occupations in a hospital - like food service workers, and workers in the laboratory [7]- are more often affected by hand eczema than workers in other professions.

Hand eczema is a problem for both the worker facing it and for the society. The physical and psychosocial burden for patients with skin diseases is comparable to patients with other chronic diseases [8]. Cost for society are related to medical consumption [9], sick leave [10] and loss of productivity [11]. Annual costs of medical care, absenteeism and disability pensions due to occupational skin diseases are estimated at € 98,1 million in the Netherlands [12].

However, hand eczema does not only lead to health effects and health care costs in the health care worker who suffers from hand eczema, but it may also have consequences for his or her patients. Several studies report that having hand eczema is a reason for non-compliance to hand hygiene protocols in hospitals [13,14]. Low adherence to hand hygiene procedures causes 20% of health care associated infections [15]. The prevalence of these infections is 6.9%, with a mortality rate of 2% and related costs of €384 million yearly [16,17]. Moreover, Staphylococcus aureus is more frequently present on the hands of patients with hand eczema than persons without it [18]. This poses a risk for workers handling food or working with patients [18]. Consequently, a reduction in the cases of hand eczema among health care workers can lead to a reduction in health care associated infections, mortality and related costs.

The high prevalence of hand eczema among health care workers - nurses, cleaners, food handlers, workers in the laboratory - and the related cost for society indicate that prevention of hand eczema is needed. For this purpose the Dutch Board for Occupational Medicine (NVAB) developed an evidence based guideline to reduce occupational hand eczema [19]. The guideline emphasizes two ways to eliminate and reduce hand eczema. First, through elimination or replacement of the contact factor responsible for the development of hand eczema [19] - in the case of health care workers this is mostly water, soap and wearing occlusive gloves [20] - and second by using preventive measures that support the skin barrier function - e.g. (cotton under) gloves and barrier creams - if avoidance of the contact factor is not possible [21,22].

Despite the problems of hand eczema among health care workers, the implementation of the recommendations from the guideline is poor. There are several reasons for this. First, many nurses - the main group of our study - consider their hand eczema as a standard side effect of their occupation. They hardly notice it anymore [23]. Further, the recommendations advise to use hand alcohol in stead of water and soap for disinfection, though a lot of nurses consider hand alcohol as violent for their skin. As a result, the compliance to this measure is low [24]. Also, a study of Held et al [25] reported difficulties towards the use of individual preventive measures, such as the use of protective gloves and recommended high fat skin care products in wet work occupations - nursing, cleaning and kitchen - in a hospital [23]. For hand hygiene measures it is known that a lack of senior role models is a contributing factor for non-compliance [14].

To implement the recommendations derived from the NVAB-guideline, effective strategies are needed aiming at the organisational and individual level. Multifaceted implementation strategies have shown to be more effective than single strategies [26]. Educational (including reminders [26]) and participatory strategies, like participatory working groups, have shown to be effective for respectively the prevention of skin diseases and musculoskeletal disorders on a small scale [21,25-28]. Further, a systematic review on the effectiveness of prevention programmes for hand dermatitis [29] found that there is moderate evidence for the effectiveness of skin care education including skin protection measures as promoted in the NVAB-guideline. In addition, using trained senior workers as role models, who stimulate the co-workers to use the preventive skin measures, has proven to be effective as an implementation strategy for preventive measures for skin disorders [25].

Although the proposed implementation strategies have proven their effectiveness, there are no studies on hand eczema using senior role models and participatory working groups for health care workers on a large scale. Therefore, a large scale intervention study is needed to evaluate the effects of using multifaceted strategies. The strategies are aimed at the implementation of a prevention program based on the NVAB-guideline. The recommendations in this guideline focus on to reduction of work-related skin disorders among health care workers. The main objective is to evaluate the effectiveness of the multifaceted implementation strategy on the frequency of (episodes of) hand eczema in health care workers. Secondary objectives are: 1) to compare effectiveness of the multifaceted strategy on adherence to the recommendations, general health status of the hands, sick leave and work productivity, and 2) to evaluate the cost-effectiveness of the multifaceted implementation strategy compared to usual practice.

## Methods/Design

### Study design

The Hands4U study is a two-armed randomised controlled trial (RCT). Randomisation is performed at the department level. Workers of the department allocated to the intervention group will receive the multifaceted implementation strategy (MIS); departments allocated to the control group will receive usual practice (no MIS). Data on all outcome measures are assessed at baseline, and 6 and 12 months after baseline. Data on the primary outcome measure (the frequency of (an episode of) eczema on the hands or forearms), as well as on adherence to the recommendations, sick leave, work productivity and health care costs are collected retrospectively every 3 months. The data collection started in April 2011.

The study protocol was approved by the Medical Ethics Committee of the VU University Medical Center. In this study, departments are included as a whole. Therefore, the Medical Ethics Committee decided that participants did not have to sign an informed consent.

### Study population and setting

Participants are health care workers recruited from the departments of three university medical hospitals in the Netherlands. In total 30.000 people are employed at these three hospitals. We only include departments were wet work (e.g. hand washing, wearing gloves) is performed. We estimated that approximately 70% of the workers in the participating hospitals perform wet work.

All departments where wet work is involved are eligible for participation in this study. When a department decides to participate, all workers from the department are invited to participate in the study. Inclusion criteria are: 1) employed at one of the participating hospitals; 2) able to fill out Dutch questionnaires; 3) aged between 18 years and 64 years; and 4) working for at least 8 hours a week. Exclusion criteria is: 1) not performing wet work (e.g. performing administrative tasks).

### Sample size

The one-year prevalence of hand eczema in health care workers in this target group is 24% according to a recent pilot study [5]. Because hand eczema is episodic in nature, repeated outcomes assessments are performed. We assume that a 25% difference in the frequency (of episodes) of hand eczema episodes during the past 3 months (primary outcome measure) is the smallest clinical and societal relevant ratio between both groups [21]. Further, the clustered randomisation on department level is taken into account. An average department is considered to have 50 workers.

Based on the results of a comparable study design [30] an intraclass correlation coefficient (ICC) of 0.73 is estimated. By using the ICC, the power analysis revealed that a sample size of 1200 workers - two groups of 600 workers - is needed to detect a 25% decrease of the frequency (of episodes) of hand eczema among the intervention group compared to the control group [21]. This difference can be detected with a power of 80% and an alpha of 0.05.

When taking into account a drop out rate of 20% a total of 1500 participants have to be recruited for this study. We assume that approximately 50% of the workers will respond to our invitation to participate and will complete the baseline questionnaires. Therefore we will invite 3000 participants in three hospitals to participate in this study.

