### Outcome measures

#### Primary outcome measure

Primary outcome is defined as the frequency of (an episode of) eczema on hands or forearms within the past three months based on questions D1 ('Have you ever had hand eczema?'), D2 ('Have you ever had eczema on your wrists or forearms?'), and D5 ('When did you last have eczema on your hands, wrists and forearms?') in the Nordic Occupational Skin Questionnaire (NOSQ-2002) [33,34]. Question D5 is measured on a four-point scale containing the options: 'I have it just now', 'Not just now, but within the past 3 months', 'Between 3 - 12 months ago' and 'More than 12 months ago'. A dichotomous variable is created using these three questions for the prevalence of hand eczema in the past three months. An interval of three months is used, because hand eczema has an episodic and recurrent course.

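### The sample size rests on a one-year prevalence of 24%, but the primary outcome covers the past three months, so the stated 80% power is not supported for that outcome

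*Protocol article*

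**What the plan says.** The Sample size section opens with its event rate: "The one-year prevalence of hand eczema in health care workers in this target group is 24% according to a recent pilot study [5". The Background shows the same figure from the same source, again as an annual one: "the 1-year prevalence of self-reported hand eczema among health care workers, including cleaners, in a university medical hospital was 24% [5".

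The smallest relevant effect is then set for a different window, as a "25% difference in the frequency (of episodes) of hand eczema episodes during the past 3 months (primary outcome measure"). The 1200 workers, 600 per group, are said to be "needed to detect a 25% decrease of the frequency (of episodes) of hand eczema among the intervention group compared to the control group", with 80% power and alpha 0.05.

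The section on the primary outcome fixes the shorter window: "Primary outcome is defined as the frequency of (an episode of) eczema on hands or forearms within the past three months". It also fixes the scale: "A dichotomous variable is created using these three questions for the prevalence of hand eczema in the past three months". One of the four answers to question D5 is "Between 3 - 12 months ago".

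The article gives no three-month rate and describes no conversion from one year to three months.

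**The concern.** A worker whose last episode was three to twelve months ago counts towards a one-year prevalence and not towards the primary outcome. With the same workers and definition, the three-month rate is therefore at most the one-year rate. It is lower as soon as anyone gives that D5 answer. The article itself calls the disease episodic, which is a reason to expect the two windows to differ.

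A 25% relative reduction of a lower rate is a smaller absolute difference: 6 percentage points from 24%, but 3.75 points from 15%. The same number of workers then gives less power. A null primary result would be read against a claim of 80% power whose only visible event rate belongs to another outcome window.

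**Working it through.** **Inputs from the article.** Prevalence 24% over one year; relative reduction 25%; 600 per arm; power 80%; alpha 0.05, two-tailed (Statistical analyses); ICC 0.73; 50 workers per department; follow-up at 3, 6, 9 and 12 months.

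**Assumed.** The three-month control rate p₁, because the article gives none. Values of 20%, 15% and 10% are shown beside 24%.

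**Step 1: the plan's own figure.** With p₁ = 0.24, p₂ = 0.75 × 0.24 = 0.18 and mean p̄ = 0.21:

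n per arm = [1.960 √(2p̄(1−p̄)) + 0.8416 √(p₁(1−p₁) + p₂(1−p₂))]² / (p₁−p₂)²

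= [1.960 × 0.5760 + 0.8416 × 0.5745]² / 0.06² ≈ 723.

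This is not 600. Three ways of bringing in the other inputs:

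- *ICC between workers of one department, as the text is ordered:* the design effect is 1 + 49 × 0.73 = 36.77, so n = 723 × 36.77 ≈ 26,585 per arm. Power at 600 per arm is about 6%.
- *ICC within a worker over k assessments:* the factor is (1 + (k−1) × 0.73)/k. For k = 3 it is 0.82 and n ≈ 593. For k = 4 it is 0.7975 and n ≈ 577, or about 603 with a continuity correction.
- *One-sided test with continuity correction, no ICC:* 602, but the article specifies two-tailed tests.

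So 600 is only approximated, and only by reinterpreting the stated inputs. These approximations use 24% against 18%, which suggests that 24% was the control rate but does not prove it.

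**Step 2: a lower control rate.** Power at n = 600 per arm is

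Φ{[(p₁−p₂)√n − 1.960 √(2p̄(1−p̄))] / √(p₁(1−p₁) + p₂(1−p₂))}.

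At 24%: (1.4697 − 1.1290)/0.5745 = 0.593, so 72%. At 15% against 11.25%: (0.9186 − 0.9360)/0.4768 = −0.037, so 49%.

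| Control rate | Intervention rate | n per arm for 80% | Power at 600 per arm |
|---|---|---|---|
| 24% | 18% | 723 | 72% |
| 20% | 15% | 906 | 63% |
| 15% | 11.25% | 1272 | 49% |
| 10% | 7.5% | 2005 | 33% |

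The table has no clustering, no repeated measures and no baseline adjustment. The gap between 80% and 72% in its first row is not due to the window. The fall from row to row is.

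**Step 3: how the design features move these figures.** Each column changes the simple comparison only as described.

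| Control rate | Four follow-ups, within-worker correlation 0.73 | The same plus baseline adjustment | Department ICC 0.01 (assumed), 50 per department, one assessment |
|---|---|---|---|
| 24% | 82% | above 99% | 55% |
| 20% | 72% | 99% | 46% |
| 15% | 58% | 96% | 35% |
| 10% | 40% | 85% | 24% |

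The second column uses effective n = 600/0.7975. The third uses the factor 0.7975 − 0.73² = 0.265, a linear approximation for a binary outcome, so it is indicative only. The fourth uses the design effect 1 + 49 × 0.01 = 1.49. In every column power falls as the control rate falls, but the level depends far more on which features are counted.

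**The case against.** The strongest objection concerns size. The article plans to adjust follow-up for the outcome at baseline. If 0.73 is a within-worker correlation, that adjustment together with four follow-ups keeps power above 80% at every assumed rate down to 10%, before clustering. This stands, subject to the linear approximation. A reader might infer that 80% power is certainly missed even before clustering is counted; the document does not support that.

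A reader might also infer that 24% must have entered the formula because 600 follows from nothing else. That goes too far. With k = 4 the formula gives 577, not 600. With baseline adjustment about 594 per arm follows from a control rate of 9%: 7.849 × (0.0819 + 0.0629)/0.0225² × 0.2646. The use of 24% is an inference from its being the only rate in the section.

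Three further points have some force. The primary outcome includes wrists and forearms while the 24% is for hand eczema, which may offset part of the drop. A recurrent disease may bring many one-year cases back within a given three months. And the undefined ICC is a larger defect: read at department level, power is about 6% even at 24%.

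None of this removes the mismatch. Repeated assessment and baseline adjustment alter the precision of a three-month outcome; they do not turn an annual rate into its control rate. Settling what 0.73 means would leave the wrong-window rate in place.

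**Conclusion.** The point holds in a limited form. The only event rate in the sample-size section is for one year, while the effect and the primary outcome are for three months, and nothing else in the article bridges the two. If 24% was the control rate, the stated 80% power for a 25% relative reduction is not supported for this outcome.

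The direction is secure for the same workers and the same definition: a lower control rate means less power for a fixed relative reduction. The size is not. In the simple comparison, 72% at a rate of 24% becomes 63%, 49% or 33% at assumed rates of 20%, 15% or 10%. Baseline adjustment and repeated measures push these figures up and department clustering pushes them down. The net power of the planned analysis cannot be settled until the three-month rate and the meaning of the ICC are stated.

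**What to change.** - Replace 24% with the three-month period prevalence of the variable built from D1, D2 and D5, and name its source. This trial's baseline questionnaire, pooled over arms, can supply it, since outcomes are assessed at baseline, before the working groups start. Whether the cited pilot recorded a three-month answer cannot be seen from the article.
- Use the term three-month period prevalence in the calculation, because the three questions give a yes/no result and do not count episodes.
- State whether 0.73 is a correlation between workers of one department or within a worker over time, and give the formula.
- Restate the power at 1200 workers, or the relative reduction detectable with 80% power, under the planned baseline-adjusted analysis with department clustering.

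The cost is one recalculation and possibly a less favourable stated power. No extra recruitment is needed, and neither the conduct of the trial nor its analysis changes.

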### Statistical analyses

All analyses are performed according to the intention to treat principle. Most analyses are performed at worker level. Two analyses are performed: 1) a crude analysis with the outcome variable measured at follow-up as the dependent variable adjusted for the outcome, measured at baseline, and 2) an analysis as above but adjusted for potential covariates (e.g. gender, age, type of work, history of hand eczema, and skin exposure). Effects of the intervention will be checked for effect modification (gender, type of exposure, number of preventive skin measures implemented). Generalised estimation equations (GEE) are used to analyse long-term results (i.e. 12 months after baseline). Furthermore, analyses at department level are performed by the use of multilevel analysis.

For all analyses a two-tailed significance level of < 0.05 is considered statistically significant. The multilevel statistical analyses are performed with MlwiN 2.0; linear and logistic regression analyses are performed with SPSS 15.0 (SPSS Inc. Chicago, Illinois, USA), and GEE analyses is performed with STATA version 7.0 (College Station, TX).

Considering the episodic nature of hand eczema, the use of transition models is necessary. In these models, the presence of hand eczema in the past three months is incorporated. The probability of getting hand eczema in workers with no hand eczema and the probability of getting no hand eczema in workers with hand eczema are modelled simultaneously by means of a logistic mixed model as is done in a study with a comparative design on low back and neck pain [32]. Transitions models will be conducted using the gllamm procedure in Stata version 10.0.

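### The sample size of 600 workers per arm cannot contain the department clustering it is said to allow for, so the stated 80% power is unsupported

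*Protocol article*

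**What the plan says.** All the design inputs are in the protocol article, section Sample size, unless noted.

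- Control prevalence: "The one-year prevalence of hand eczema in health care workers in this target group is 24% according to a recent pilot study".
- Target: 1200 workers, 600 per group, are "needed to detect a 25% decrease of the frequency (of episodes) of hand eczema among the intervention group compared to the control group".
- Clustering: "Further, the clustered randomisation on department level is taken into account. An average department is considered to have 50 workers".
- Correlation: "Based on the results of a comparable study design [30] an intraclass correlation coefficient (ICC) of 0.73 is estimated". The section does not say whether this correlates workers within a department or repeated answers from one worker. No other ICC is given.
- Conclusion: "This difference can be detected with a power of 80% and an alpha of 0.05".
- Sidedness, from Statistical analyses: "For all analyses a two-tailed significance level of < 0.05 is considered statistically significant".

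The Sample size section also mentions repeated outcome assessments just before the calculation, and assumes 50% response and 20% dropout. Statistical analyses specifies that both the crude and the adjusted analysis adjust for the outcome at baseline. The section on the working groups expects about 30 of them, one per intervention department.

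**The concern.** An allowance for cluster randomisation makes a required sample size larger. Here the stated number is smaller than the one for an individually randomised trial with a single measurement. The 0.73 must therefore have reduced the total or not entered it, and neither fits the claim that clustering was allowed for.

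The 25% decrease is described as the smallest relevant difference, so 80% power for it is the benchmark against which a null result will be read. If that figure ignores departments, readers may take a null result as stronger evidence against a 25% reduction than the design can give.

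**Working it through.** **Inputs.** 24% versus 18% (24% × 0.75), two-sided 0.05, 80% power, 600 per arm. Follow-ups at 3, 6, 9 and 12 months (Abstract), so k = 4. Analysed workers per department: 50 × 0.5 × 0.8 = 20. Departments: 3000 invited / 50 = 60, which agrees with about 30 intervention working groups at 1:1; 1200 / 60 = 20.

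**1. No clustering, one measurement.** With pooled variance under the null,

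n = [1.96·√(2·0.21·0.79) + 0.8416·√(0.24·0.76 + 0.18·0.82)]² / 0.06² = (1.1290 + 0.4835)² / 0.0036 ≈ 722 per arm.

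Power for 600 per arm with variance factor F is Φ[(0.06·√(600/F) − 1.1290) / 0.5745]. With F = 1 it is 72%.

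**2. 0.73 as the department ICC.** F = 1 + (m − 1)·0.73.
- m = 50: F = 36.8, 1200 workers count as about 33, power about 6%.
- m = 20: F = 14.9, 1200 workers count as about 81, power about 10%.

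Neither comes near 80%.

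**3. 0.73 as a within-worker correlation, no department term.** F = (1 + (k − 1)·0.73)/k.
- k = 4: F = 0.7975, 722 × 0.7975 = 576 per arm. With a continuity correction the result is about 603. Power at 600 without the correction is 81.6%.
- k = 3: F = 0.82, 722 × 0.82 = 592 per arm.

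These come close to the stated 600.

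**4. Adding a department term.** The document gives no separate department ICC, so 0.01 to 0.05 is an assumption. Two versions of F are shown, both taking 0.73 as the within-worker correlation:
- without credit for baseline adjustment: F = 0.7975 + (m − 1)·ICC;
- with credit: F = 0.7975 − 0.73² + (m − 1)·ICC = 0.2646 + (m − 1)·ICC. This is a linear approximation for a binary outcome and assumes that 0.73 also holds between baseline and follow-up.

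| Analysed per department | Department ICC | Power, no baseline credit | Power, baseline credit |
|---|---|---|---|
| 20 | 0.01 | 73% | 97% |
| 20 | 0.02 | 65% | 89% |
| 20 | 0.05 | 49% | 64% |
| 50 | 0.01 | 61% | 84% |
| 50 | 0.02 | 48% | 63% |
| 50 | 0.05 | 29% | 34% |

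At 20 per department, power falls below 80% above an ICC of about 0.002 without the credit and about 0.03 with it.

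**5. The remaining steps.** 1200 / 0.8 = 1500 and 1500 / 0.5 = 3000 are correct.

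**The case against.** The strongest defence is that the power loss is not established. The planned analyses adjust for baseline eczema. If the within-worker correlation really is 0.73, that adjustment removes much of the variance, and at 20 analysed per department power could exceed 80% at department ICCs of 0.01 and 0.02. Prestratification by risk and patient contact, and covariates such as type of work, may shrink the between-department variance further. This stands. A reader might infer that true power is well below 80%, but the document gives neither the department ICC nor the baseline correlation needed to show it.

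Nor is it established how 600 was obtained. A reader might infer that 0.73 was certainly used as a within-worker correlation. That is only an inference from several near-matches. A one-sided, continuity-corrected calculation with no ICC also gives about 602 per arm, although it conflicts with the two-tailed level and with the statement that the ICC was used. For the same reason, the 6% to 10% figures show what a literal department reading would imply. They do not estimate the trial's power.

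The figure of 50 workers is not itself an error, since it agrees with the department size in the working-group section. It is only not the number analysed.

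None of this rescues the paragraph. The section claims no gain from baseline adjustment, and such a gain would not make the clustering statement true. The objection is to what the article states, not to detail left to a fuller document.

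**Conclusion.** The point holds as an internal contradiction. For 24% versus 18%, two-sided, 600 per arm is below the 722 needed before any clustering, so the total cannot include a department design effect. The 80% is unsupported for a department-randomised design on either reading of the 0.73.

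The size of any shortfall is open. With 20 analysed per department and an assumed department ICC of 0.01 to 0.05, power runs from 73% down to 49% without baseline credit and from about 97% down to 64% with it.

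The conclusion rests on treating the target as a comparison of two proportions, which fits the dichotomous primary outcome, and on 24%, the only control prevalence given. That is a one-year figure, while the outcome covers three months. A lower three-month prevalence would raise the unclustered requirement; an assumed 18%, for example, gives about 1028 per arm.

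**What to change.** Rewrite the calculation paragraph in the Sample size section:

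1. State whether the 0.73 refers to workers within a department or to repeated assessments within a worker.
2. Give a separate department ICC with a range and its basis, together with the expected analysed cluster size (about 20 after response and dropout).
3. Recompute for the planned repeated-measures, baseline-adjusted analysis with a department term, and state the assumed baseline correlation.
4. Replace the 80% statement with the power, or the detectable reduction, that 1200 workers in about 60 departments deliver over that range.

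The cost is one paragraph and one recalculation. Recruitment, randomisation and data collection do not change. The drawback is that the stated power may become less favourable.
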